### Data Management and Safety Monitoring

The REDCap (Research Electronic Data Capture; Vanderbilt University) platform will be used for data management. To ensure integrity and blinding, the blinded team enters assessment data into a restricted partition, whereas the unblinded team logs adherence and physiological data separately. All manual entries from paper forms undergo a double-check verification process by a supervisor. Data are stored on secure servers with regular backups, and the final dataset will remain locked until the analysis plan is finalized.

Regarding safety monitoring, given the low-risk nature of the exergame intervention, a formal external data monitoring committee was not convened. Instead, continuous monitoring for cybersickness and physical discomfort is conducted by the unblinded team supervisors and reviewed weekly by the steering committee. Participants reporting persistent adverse effects are withdrawn according to established safety protocols.

## Results

This trial is ongoing. Funding was granted in October 2024. Recruitment commenced in June 2024 across 2 sites: Hospital de Clínicas de Porto Alegre (Rio Grande do Sul) and Centro Escola de Especialidades Médicas (São Paulo). As of April 2026, 58 participants have been enrolled (n=35, 60.3% in Rio Grande do Sul and n=23, 39.7% in São Paulo), of whom 46 (79.3%) have completed the full intervention protocol. Data collection is expected to be completed by October 2026, with results anticipated by December 2026. No interim analyses have been conducted.

## Discussion

This randomized clinical trial evaluates the efficacy of an HIIT-based VR exergame as a novel nonpharmacological intervention for adolescents with ADHD, a population for whom effective and engaging treatment options remain limited. To our knowledge, this is the first rigorously controlled trial to investigate an HIIT-based VR intervention specifically tailored for adolescents with ADHD and delivered in a remotely monitored, home-based format. In addition to testing the clinical effectiveness of this intervention, the study incorporates a methodological design that allows for secondary exploration of whether potential benefits are primarily driven by physiological exertion, immersive VR engagement, or their interaction.

Several features strengthen the methodological rigor of this protocol. The use of an active VR control condition represents a substantial advancement over passive or nonequivalent comparators frequently used in prior studies [26], thereby improving causal inference regarding the contribution of vigorous physiological exertion beyond VR immersion and digital engagement alone to executive function outcomes. The Move Sapiens HIIT protocol has been validated via a pilot test [11], demonstrating its capacity to elicit vigorous cardiovascular and metabolic responses comparable to traditional high-intensity training while maintaining high intrinsic motivation. Focusing on adolescents aged 12 to 17 years targets a developmental stage characterized by distinctive motivational profiles and reduced adherence to pharmacological treatments. Finally, home-based delivery provides critical data on feasibility and effectiveness beyond laboratory-controlled environments. The intervention will be administered in participants’ own homes and daily routines, representing an essential step toward future clinical translation and scalability.

Several limitations should be acknowledged. The single-blind design introduces the possibility of expectancy effects; however, this risk is partially mitigated by the use of an engaging active control condition matched for novelty and immersion. Notably, expectancy bias may disproportionately affect the parent-reported inattention outcome given that parents are aware of their children’s group assignment. The inclusion of the go/no-go task as a co–primary objective performance measure allows for a complementary assessment that is less susceptible to expectancy effects as it is independent of rater expectations. Furthermore, the 2 study arms differ not only in metabolic load but also in gross motor demand and task experience as the intervention requires full-body movement whereas the control condition involves joystick-only interaction. These differences are inherent to ecologically valid comparisons of this nature and preclude definitive attribution of any observed effects to a single component of the intervention. The 4-week intervention period may be insufficient to induce durable neuroplastic changes or sustained behavioral adaptations as longer intervention durations have been associated with stronger consolidation of executive function gains in meta-analytic studies. Nevertheless, budgetary and logistical constraints limited the feasibility of implementing longer protocols, and the selected intervention length is consistent with the duration most commonly used in studies evaluating HIIT, neuromodulation, and computerized cognitive training for ADHD [27]. Excluding participants currently receiving pharmacological treatment limits generalizability but was necessary to isolate the specific effects of the exercise intervention. Although parent-reported inattention outcomes may be subject to rater bias, this limitation is offset by the inclusion of objective, performance-based measures of inhibitory control, which have demonstrated sensitivity to high-intensity exercise interventions. Finally, while home-based delivery precludes direct supervision, structured remote monitoring provides systematic indexes of adherence and training intensity, thereby ensuring intervention fidelity.

If the study demonstrates significant improvements in inhibitory control and inattention in the HIIT VR group compared with the nonexercise VR control, these findings will support the clinical efficacy of an HIIT-based VR exergame as a novel, engaging nonpharmacological intervention for adolescents with ADHD. Such results would have important implications for expanding treatment options in a population characterized by limited adherence to existing therapies. Conversely, if no differential effects are observed between groups, this would suggest that immersive VR engagement itself may represent a key therapeutic component, providing valuable insights for the design of future digital and game-based interventions. By evaluating a developmentally appropriate, home-based HIIT VR intervention within a rigorously controlled design, this trial has the potential to advance both the clinical and methodological evidence base for nonpharmacological treatments in ADHD. Results will be disseminated through peer-reviewed publications and scientific conferences regardless of the direction of the findings.

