#### Phase 1: Recruitment and Baseline (Weeks 0 to 1)

Potential participants undergo an initial online screening. After provision of informed consent, a comprehensive psychiatric evaluation is conducted by 2 child and adolescent psychiatrists to confirm eligibility, establish the ADHD diagnosis, and screen for psychiatric comorbidities using the Schedule for Affective Disorders and Schizophrenia for School-Aged Children [13]. Eligible adolescents then proceed to the first in-person visit (visit 1), which includes the complete baseline neuropsychological assessment, physiological baseline recording (heart rate), and self-report questionnaires (Pittsburgh Sleep Quality Index and 7-item Generalized Anxiety Disorder scale). Additionally, participants experience their first exposure to the VR environment (habituation) to assess tolerability and equipment fit without engaging in the intervention protocol.

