#### Phase 2: Familiarization and Safety (Week 1)

Following baseline, participants complete 3 consecutive days of supervised familiarization (visits 2 to 4) in the research center. In these sessions, participants learn to operate the Meta Quest 2 and 3S headsets and practice the specific game version corresponding to their allocation (HIIT VR or control VR). During these sessions, the research staff continuously monitors safety parameters, including heart rate (via Polar H10 sensors) and potential cybersickness symptoms. The final familiarization session includes a review of the participants’ daily routine to establish the optimal time for home practice and signing of the equipment responsibility form.

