#### Phase 3: Home-Based Intervention (Weeks 2 to 5)

Participants take the VR headset home for a 4-week period. The protocol requires 1 session per day, 5 days per week (20 sessions in total). Adherence is strictly monitored via WhatsApp. Immediately after each session, participants must send (1) a screenshot of their final game score and (2) their rating on the Borg scale of perceived exertion (6 to 20). We enforce strict adherence to ensure intervention fidelity. Participants who miss a scheduled weekday session are required to make up the missed training on the weekend to maintain the total weekly dose. Three unjustified absences or failure to complete the required number of sessions despite makeup opportunities will result in exclusion from the study.

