**Other prespecified domains**					
	Physiological exercise intensity	Polar H10 HR^e^ monitor (processed using the Kubios software)		Average HR, HR_max_^f^, HRR^g^ (Δ in bpm^h^ over 5 min), and HRV^i^ indexes	
	Game experience	GEQ^j^		Subscale scores and/or total experience score	
	VR discomfort	SSQ^k^		Incidence or severity of nausea, oculomotor issues, and disorientation	
	Enjoyment	PACES^l^		Total enjoyment score	

^a^SNAP-IV: Swanson, Nolan, and Pelham Rating Scale version IV.

^b^MOXO-CPT: MOXO continuous performance test.

^c^PSQI: Pittsburgh Sleep Quality Index.

^d^GAD-7: 7-item Generalized Anxiety Disorder scale.

^e^HR: heart rate.

^f^HR_max_: maximum heart rate.

^g^HRR: heart rate reserve.

^h^bpm: beats per minute.

^i^HRV: HR variability.

^j^GEQ: Game Experience Questionnaire.

^k^SSQ: Simulator Sickness Questionnaire.

^l^PACES: Physical Activity Enjoyment Scale.

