#### Additional Measures

Additional measures comprise, first, physiological load and perceived exertion. Heart rate is monitored continuously during laboratory sessions using Polar H10 sensors. Additionally, we collect the Borg rating of perceived exertion (6 to 20) after every session (laboratory and home) to quantify training intensity [22].

The second additional measure is user experience and tolerability. VR-specific effects are assessed after exposure using the Simulator Sickness Questionnaire for adverse effects [23], the Physical Activity Enjoyment Scale for engagement [24], and the Game Experience Questionnaire for usability [25].

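### Exertion in the 20 home sessions is indexed only by self-report, so fidelity to the vigorous dose is not ensured and the planned reading of a null result needs a condition

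*Protocol article*

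**What the plan says.** Training schedule (Methods, Phase 3): "The protocol requires 1 session per day, 5 days per week (20 sessions in total"), all in the home phase.

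Reports from home (same section): after each session the participant sends, by messaging app, "a screenshot of their final game score and (2) their rating on the Borg scale of perceived exertion (6 to 20").

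Heart rate (Methods, Additional Measures): "Heart rate is monitored continuously during laboratory sessions using Polar H10 sensors". The same section says that Borg ratings are taken after laboratory and home sessions alike. Phase 2 states that "participants complete 3 consecutive days of supervised familiarization (visits 2 to 4) in the research center", and that there "the research staff continuously monitors safety parameters, including heart rate (via Polar H10 sensors) and potential cybersickness symptoms". Phase 1 adds a "physiological baseline recording (heart rate") at visit 1.

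Claim (Discussion, limitations): after granting that home delivery rules out direct supervision, the article says that "structured remote monitoring provides systematic indexes of adherence and training intensity, thereby ensuring intervention fidelity".

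Use of the claim (Discussion, closing paragraph): if the arms do not differ, the article would take this as a sign that VR engagement itself may be an important therapeutic ingredient.

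Table 1, under the other prespecified domains: HRR has as its metric a change in beats per minute over 5 minutes, and the footnote reads "HRR: heart rate reserve".

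**The concern.** The control arm keeps the VR environment and removes the exertion, so the contrast between arms carries information about vigorous exertion only to the extent that exertion was delivered. The sessions that deliver it are unsupervised. The only intensity measure there is a rating that participants give of themselves and that nothing in the article verifies.

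A null result then has at least two explanations: vigorous exertion adds nothing to VR, or effort at home fell below vigorous and the arms were less different than intended. The Discussion takes the first route. Its limitations paragraph lists differences in motor demand and task experience, but not under-delivered intensity. On that point it offers an assurance where a limitation belongs.

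**Working it through.** **1. The plan's own session figures reproduce.**
- Sessions: 5 per week × 4 weeks = 20.
- Session length: 12 × (16 s + 20 s) = 432 s = 7 min 12 s, as stated under Interventions.

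**2. Which measure covers which session.**

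| Contact | Sessions with the allocated game | Heart rate described | Borg planned |
|---|---|---|---|
| Visit 1 (baseline, VR habituation only) | 0 | baseline recording | not stated |
| Visits 2 to 4 (familiarization) | 3 | yes | yes |
| Home, weeks 2 to 5 | 20 | no | yes |

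- Training sessions with heart rate: 0 / 20 = 0%.
- All sessions with the allocated game, counting familiarization: 3 / (3 + 20) = 3 / 23 = 13%, all before home training starts.
- Training sessions with a planned Borg rating and score screenshot: 20 / 20 = 100%.

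**3. Where the evidence of vigorous effort comes from.** The heart rates given under Interventions (mean about 161, peak about 182 beats per minute) come from a separate pilot crossover study. They show what the format can elicit, not what unsupervised participants in this trial did over four weeks.

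**4. From index to assurance.** The Discussion sentence has two parts. The first, that remote monitoring yields systematic indexes, agrees with Phase 3 and Additional Measures. The second, that fidelity is thereby ensured, does not follow: a subjective rating can suggest that effort was high or low, but it cannot guarantee it.

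**5. From assurance to interpretation.** The closing paragraph's account of a null result needs a premise that the article does not state: that home effort was vigorous in the HIIT arm and clearly higher than in the control arm. The Borg ratings bear on this premise, but the article does not link them to the interpretation.

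**6. HRR, a separate matter.** A heart rate reserve is maximum minus resting rate. A change over 5 minutes describes recovery. Table 1 puts both under one label. This is a laboratory metric and plays no part in steps 1 to 5.

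**The case against.** The strongest case on the other side is that the article already provides what it claims. Indexes of adherence and intensity are planned for every home session, the lack of supervision is acknowledged, and a detailed manipulation check can be left to an analysis plan that is not shown. Much of this stands. The absence of a check from an article is not itself an error. What remains is an explicit statement that fidelity is ensured, and an explicit reading of a null result that relies on it.

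Several stronger readings are tempting, and the documents do not support them:

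- *That intensity and fidelity are unsupported for every training session.* A subjective index and a screenshot are planned for all 20.
- *That the HRR label weakens the home claim, or leaves the trial without an intensity metric.* HRR concerns laboratory data, and average and maximum heart rate stand in the same row of Table 1.
- *That a positive result would be misattributed to exertion because of this gap.* The limitations paragraph already says that no single component can be credited definitively, and home heart rate would not remove the differences in movement and task.
- *That the game score says nothing about exertion.* Scoring is not described. HIIT players must physically strike and dodge, so the score may partly reflect movement.
- *That the exclusion rule pushes participants to inflate Borg ratings.* The rule concerns missed sessions. No Borg threshold is attached to it, and the article does not say what participants are told about it.

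**Conclusion.** The point holds in a limited form and is worth acting on. For 20 of 20 training sessions, intensity is indexed by unsupervised self-report; for 0 of 20 is heart rate described. Fidelity to the vigorous dose is therefore monitored, not ensured, and the null interpretation in the closing paragraph of the Discussion is conditional on something the article treats as settled. The consequence falls mainly on a null result. The design, the randomized comparison and the primary outcomes are unaffected.

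This assumes that the article's text is complete about where heart rate is recorded. Figure 2 and any full protocol were not available. If home heart rate is in fact collected, the article should say so and the point largely falls away.

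The HRR inconsistency is a separate, minor labelling error.

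**What to change.** 1. **Discussion, limitations.** Replace the statement that fidelity is ensured with one saying that intensity at home rests on self-reported exertion.
2. **Manipulation check, fixed before the dataset is unlocked.** Summarize home Borg ratings by arm and week. In the HIIT arm only, compare them with each participant's own laboratory Borg ratings and heart rate. Summarize controls descriptively: they use a joystick and have no vigorous laboratory effort to compare with.
3. **Discussion, closing paragraph.** Make the null interpretation conditional on the check showing that vigorous effort was sustained at home and separated the arms. Otherwise, report that under-delivered intensity remains a possible explanation.
4. **Table 1, separately.** Correct the HRR label so that it matches the 5-minute metric.

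The timing allows this. The article says that the final dataset stays locked until the analysis plan is finalized, that data collection runs to October 2026, and that no interim analysis has been done. No new sensors or visits are needed.

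Costs:
- The check is approximate. It has at most three laboratory Borg ratings per participant and still depends on self-report at home.
- It should not be built on percentage of heart rate reserve, because the article states neither a maximal test nor that the visit 1 recording was taken at rest.
- Borg ratings by arm may reveal to the analyst which coded group is which, so the check is best run after the primary analysis or by someone else.
- The fidelity claim becomes weaker.

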**Methods:**

This multisite, parallel-group, single-blind randomized clinical trial will recruit 98 adolescents aged 12 to 17 years with a confirmed diagnosis of ADHD according to the *Diagnostic and Statistical Manual of Mental Disorders, Fifth Edition*, from 2 outpatient centers in Brazil. Participants will be allocated 1:1 to an HIIT-based VR exergame intervention (Move Sapiens) or an active control condition using the same VR platform without vigorous physical exertion. The intervention comprises 20 sessions over 4 weeks delivered in a home-based format following supervised laboratory familiarization. Primary outcomes are Swanson, Nolan, and Pelham Rating Scale version IV inattention subscale scores and go/no-go commission errors. Secondary outcomes include working memory, cognitive flexibility, processing speed, impulsivity, sleep quality, and anxiety symptoms. Analyses will follow an intention-to-treat approach using linear mixed-effects models.

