## Methods

### Study Design and Setting

This study is designed as a multisite, parallel-group, single-blind randomized clinical trial with a 1:1 allocation ratio reported in accordance with the SPIRIT (Standard Protocol Items: Recommendations for Interventional Trials) 2025 guidelines (version 1.0; March 2026). The trial aims to demonstrate the superiority of the active intervention over the control condition. We will collect data at 2 research centers in Brazil: Hospital de Clínicas de Porto Alegre (Rio Grande do Sul) and Centro Escola de Especialidades Médicas in Indaiatuba (São Paulo).

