#### Eligibility Criteria

We will include participants aged 12 to 17 years with a confirmed diagnosis of ADHD according to the Diagnostic and Statistical Manual of Mental Disorders, Fifth Edition. Additionally, participants must demonstrate a score of 12 or higher on the Swanson, Nolan, and Pelham Rating Scale version IV inattention subscale. Regarding medication status, we will include participants who are either medication naive or not currently using ADHD medication (having discontinued use prior to study enrollment for at least 30 days). Importantly, the study does not request or encourage the discontinuation of prescribed medication for research purposes. However, participants who initiate or resume pharmacological treatment during the study period for clinical reasons will be withdrawn from the study to avoid confounding effects.

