#### Control Condition (Nonexercise VR)

Participants assigned to the control group will use an adapted nonexercise version of Move Sapiens. This version preserves the same immersive VR environment, visual assets, and sound design but removes all components of physical exertion. Interaction occurs exclusively through a joystick. Session duration and frequency mirror those of the intervention group. This design enables examination of the specific contribution of vigorous physical exertion to the observed outcomes while controlling for VR immersion and digital engagement, both of which are preserved across conditions.

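### The Discussion reads a null result as pointing to a benefit of VR, and offers to explore VR and interaction effects, but with VR in both arms the trial cannot inform either

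*Protocol article*

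**What the plan says.** All references are to the protocol article.

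- **Discussion, closing paragraph (null result):** "if no differential effects are observed between groups, this would suggest that immersive VR engagement itself may represent a key therapeutic component". The article gives no other reading of a null result.
- **Discussion, opening paragraph (attribution):** the design is said to allow "secondary exploration of whether potential benefits are primarily driven by physiological exertion, immersive VR engagement, or their interaction".
- **Abstract, Methods (arms):** "Participants will be allocated 1:1 to an HIIT-based VR exergame intervention (Move Sapiens) or an active control condition using the same VR platform".
- **Control Condition (Nonexercise VR):** the comparison is described as "controlling for VR immersion and digital engagement, both of which are preserved across conditions".
- **Study Design and Setting (hypothesis):** "The trial aims to demonstrate the superiority of the active intervention over the control condition". The article states no equivalence margin.
- **Statistical Methods:** the modelled effect is the treatment-by-time interaction between the two arms.
- **Discussion, limitations:** the arms also differ in gross motor demand and task experience, and these differences "preclude definitive attribution of any observed effects to a single component of the intervention".

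**The concern.** Two statements in the Discussion go beyond what the design can show.

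The first concerns attribution. To learn whether VR engagement drives a benefit, or whether VR and exertion interact, some participants must go without VR. None do.

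The second concerns the null result. Failure to show that one version beats the other says nothing about whether either works. The article nevertheless attaches a favourable message about VR to that outcome while the trial is still running, and presents it as guidance for designing later digital interventions. If the sentence is carried into the results paper, an unsuccessful superiority test could be reported as support for VR on no evidence from this trial.

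**Working it through.** **1. What can be estimated.** Lay the trial out as exertion (yes/no) by VR (yes/no), with μ for the mean change in each cell:

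| | VR | No VR |
|---|---|---|
| Exertion | μ11: exergame arm | μ10: not in trial |
| No exertion | μ01: joystick arm | μ00: not in trial |

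- Exercise version versus joystick version, given VR: μ11 − μ01. Both cells are observed, so this is estimable. It carries the differences in movement and task experience that the limitations paragraph concedes.
- Effect of VR: μ01 − μ00 without exertion, or μ11 − μ10 with exertion. Each needs an empty cell.
- Exertion-by-VR interaction: (μ11 − μ01) − (μ10 − μ00). This needs both empty cells.

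The last two are not identified whatever the sample size or the model.

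**2. What a null difference is compatible with.** Suppose μ11 and μ01 really are equal. That fits VR helping in both arms, and equally fits nothing helping in either. Improvement from baseline in both arms would not settle the matter, because other sources of change are present:

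- regression to the mean on SNAP-IV inattention, since for entry "participants must demonstrate a score of 12 or higher" (Eligibility Criteria);
- practice, since the same assessments are repeated at the final visit (Phase 4);
- expectancy on the parent report, since parents know the allocation (Discussion, limitations).

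Randomisation balances such influences between arms. It does not remove them from change within an arm.

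**3. How often a null result would hide a real effect.** Inputs from Sample Size and Statistical Methods: standardised effect 0.50, two-sided α 0.05, power 0.80, 30% attrition, 49 per arm. Completers per arm: 49 × 0.70 = 34.3, taken as 34.

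The plan's figure first. An unadjusted comparison needs n = 2(1.960 + 0.842)² / 0.50² = 62.8, or 63 per arm. That is 126 in total, and 126 / 0.70 = 180 after attrition, not 98. A baseline-adjusted comparison with an unstated correlation of about 0.68 does give 98: 62.8 × (1 − 0.68²) = 33.8, or 34 per arm, and 34 / 0.70 = 48.6, or 49 per arm. The article does not state its basis, so both cases are carried forward. The sample size itself is a separate matter.

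Chance of a non-significant result on one outcome when the true effect is 0.50:

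| Basis | Power | Chance of missing it |
|---|---|---|
| Stated design power | 0.80 | 20% |
| Unadjusted t-test, 49 per arm | 0.688 | 31% |
| Unadjusted t-test, 34 per arm | 0.529 | 47% |

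Half-width of the 95% confidence interval for the standardised difference, unadjusted, t × √(2/n):

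- 34 per arm: 1.997 × √(2/34) = 1.997 × 0.2425 = 0.48 SD
- 49 per arm: 1.985 × √(2/49) = 1.985 × 0.2020 = 0.40 SD

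**4. Could the trial show that the arms are similar?** Take an illustrative margin of ±0.50 SD (an assumption; none is stated) and a true difference of zero. The approximate power of two one-sided 5% tests is 2Φ(0.50/SE − 1.645) − 1. With SE 0.2425 (34 per arm) this is 32%; with SE 0.2020 (49 per arm) it is 59%. On this unadjusted basis, similarity itself would be hard to establish, quite apart from what causes it.

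**The case against.** The best defence is that this is hedged Discussion prose. The text says a null would suggest that VR may be a key component, and it offers only secondary exploration. No analysis of a VR effect, of within-arm change or of equivalence is specified, and no decision rule depends on these sentences. That stands as a limit on the point: a reader might infer that the plan will formally treat a non-significant result as proof that VR works, and the article does not say so. Hedging does not rescue the inference, however, because the design gives no evidence about VR in either direction.

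Other strong readings are also unsupported:

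- **That the article contradicts itself.** The limitations paragraph rules out only definitive attribution of observed effects. Tentative exploration can coexist with that, and the paragraph is silent on null results. By the same token, it does not repair the null-result sentence.
- **That a null result is likely.** At the assumed effect of 0.50, every figure above is below 50%, and the higher ones rest on an unadjusted t-test, whereas the article specifies mixed models. The figures are also per outcome. With 34 per arm and 0.50 on both primary outcomes, the chance that both are non-significant runs from about 22% (independent: 0.47 × 0.47) to 47% (perfectly correlated).
- **That most null results could not exclude 0.50.** With a half-width of 0.484, this happens when the estimate exceeds 0.016. For 34 per arm that is about 47% of null results if the true difference is zero, and about 85% if it is 0.30. It depends on the unknown truth.
- **That other sections need rewriting.** The Abstract's Conclusions and the Control Condition section describe the contrast that the trial does make. The entry threshold is not a defect.

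**Conclusion.** The point holds for two sentences in the Discussion. The opening paragraph credits the design with a property it lacks: neither the VR effect nor the exertion-by-VR interaction can be estimated with VR in both arms. The closing paragraph draws from a null superiority result a suggestion about VR that does not follow.

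Both conclusions rest on the arm structure alone and need no assumption about power. The numbers only show that a missed effect is a realistic alternative explanation: 20% per outcome if the design power is achieved, and 31% to 47% if the analysis behaves like an unadjusted t-test with 49 to 34 per arm. The primary comparison and the planned model are unaffected. What changes is what the trial may say if no difference is shown.

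**What to change.** **Discussion, closing paragraph.** Replace the null-result sentence with: *If no difference is shown, the result will be reported as inconclusive, or as bounding the added effect of the exercise version over the joystick version by its 95% confidence interval. It will not be read as evidence that VR is therapeutic, because the trial has no non-VR control.*

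**Discussion, opening paragraph.** Delete the reference to VR engagement and to the interaction. Limit the claim to: *the effect of the exercise version compared with the joystick version when both are delivered in VR*. This agrees with the caveat in the limitations paragraph.

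If the sponsor wishes to claim similarity of the two versions, a margin has to be specified beforehand. Even then the claim would concern the difference between versions, not the effect of VR.

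No change is needed to the Abstract's Conclusions, Eligibility Criteria or Control Condition section on this account.

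**Cost.** Wording only, with no change to conduct, data or analysis. The trial gives up a claim that it cannot support.
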